### 2.6 Data analysis

Our main analysis will be intention to treat [86]. There will be no subgroup or interim analysis.

#### Pilot study

We will use a paired t test to examine for differences in headache score when subjects are randomized to intermittent ISMO compared to the same subjects randomized to intermittent NTG.

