## 2.0 Methods

### 2.1 Study design

This research proposal consists of two placebo controlled trials: a four week pilot study and a 27 month main study. The main study will be preceded by a one week nitrate run-in phase. Both the pilot and main study will recruit healthy postmenopausal women, 50 years of age and older, with lumbar spine BMD T scores between 0 and -2.0. The aim of the pilot study is to determine the best tolerated preparation of nitrate for future studies. We will assess eligibility for the pilot study by questionnaire, focused physical examination, electrocardiogram (ECG) and review of most recent BMD measurements. Subjects (n = 22) will be randomly assigned to intermittent NTG at 15 mg/day and intermittent ISMO at 20 mg/day, each for one week. The order of the treatments will be random, accompanied by a placebo control (identical in sight and smell to the active treatment). In between each treatment there will be a two week washout period. Subjects will record the severity of headaches upon awakening every day for four weeks using a visual analog scale (VAS). We will calculate the mean headache score for each subject over both seven day treatment periods and then the mean headache score considering all subjects for each of the NTG and ISMO treatment periods.

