### 2.2 Trial interventions

#### Pilot study

Subjects will receive NTG ointment; at 15 mg/day (one inch of 2% ointment applied to the upper arm) for one week and ISMO at 20 mg/day for one week. The order of treatments will be randomized. In between each treatment there will be a two week washout. The washout exceeds ten half lives of NTG (one hour) and ISMO (five hours) and will eliminate any carryover effects [54-57]. Subjects who report headaches during the wash out will be excluded from the second treatment phase and considered as drop outs in our analysis. We have considered drop outs in our sample size calculations. Both treatments will be administered with placebo (tablet or paste, as appropriate). Subjects will receive standard instructions on how to take the tablet (at bed time with a glass of water; as was given in our earlier study) and patch (apply it first thing in the morning; as was given in the earlier study).

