### 2.4 Study outcomes

#### Pilot study

The primary outcome will be mean headache score associated with each of intermittent NTG and ISMO use. Subjects will be given four seven day diaries, with a VAS for each day of both treatment periods and the wash out period. Subjects will rate their headache upon awakening on a daily basis; our previous study demonstrated that subjects randomized to ISMO who developed headaches reported that the headache was most severe upon awakening and gradually subsided over the day [43]. The VAS uses a 100 mm continuous horizontal line with the left pole labeled "no headache" and the right pole labeled "terrible headache"; subjects will be instructed to draw a vertical line intersecting the VAS indicating the severity of their morning headache. We will calculate the mean headache score with intermittent NTG and intermittent ISMO for each subject. Then we will calculate the mean headache score for all subjects when taking ISMO and when taking NTG. The nitrate that gives the lowest mean headache score will be used in our main study. Our earlier work indicates that the nitrate formulation associated with the most severe headaches will result in the greatest number of drop outs [30]. The VAS can detect subtle changes in subjective complaints (i.e. headache), has documented reliability, and has been used in several studies designed to study the effects of NTG ointment on headache in healthy women [56,57].

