### 2.5 Sample size

#### Pilot study

We wish to detect at least 15 units difference in headache score using the VAS between the intermittent NTG and ISMO groups, which is consistent with a modest effect [57]. We assumed a power of 90% and two sided alpha of 0.05, a standard deviation of 27.78 (based on studies using the VAS to report headaches in healthy women), [56,57] and a small correlation of 0.5 among the repeated measurements [77]. Based on these assumptions, the number of subjects needed for comparing (paired) the mean headache scores for two groups is 20 subjects (Table 4A). We will increase this number by 10%, to account for women who develop headaches that continue into the washout period and cannot go on to the second treatment. Note that this is a conservative approach, in our earlier study all women who developed headaches reported that when they stopped the treatment the headache resolved within 24 hours. Based on these assumptions, we will require 22 subjects for our pilot study.

**Table 4A T4:** Formula used for sample size calculation for pilot study.

*n *= (*Z*_1-*α*/2 _+ *Z*_1-*β*_)^2 ^{1 + (*n *- 1)*ρ*}/(*n*Δ^2^), where *n *= 7, *ρ *= 0.2, Δ = , *β *= 0.1.

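### The pilot crossover is tested with a paired t test and the nitrate chosen on raw means; both ignore period, which costs power and, if the analysed orders are unequal, shifts the estimate conditionally on that split

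*Protocol article*

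**What the plan says.** The pilot is a two-period crossover. Each woman takes nitroglycerin ointment (NTG) for one week and isosorbide mononitrate (ISMO) for one week. Section 2.1 states: "In between each treatment there will be a two week washout period". The treatment weeks are therefore weeks 1 and 4. On allocation, Section 2.2 (Pilot study) states: "The order of treatments will be randomized".

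The analysis and the decision rule are both fixed in the text:

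- Test (Section 2.6, Pilot study): "We will use a paired t test to examine for differences in headache score".
- Summary (Section 2.4, Pilot study): "Then we will calculate the mean headache score for all subjects when taking ISMO and when taking NTG".
- Choice (Section 2.4, Pilot study): "The nitrate that gives the lowest mean headache score will be used in our main study".

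On time-related effects, Section 2.2 argues only that the washout "will eliminate any carryover effects". It also says: "Subjects who report headaches during the wash out will be excluded from the second treatment phase". Those women count as drop-outs. Section 3.0 reports the pilot as completed, with significantly lower headache scores on NTG, and the main study as using NTG.

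**The concern.** Headache scores may differ between weeks 1 and 4 for reasons unrelated to which drug is taken, such as expectation or familiarity with the diary. The half-life argument in Section 2.2 deals with residual drug and does not exclude this.

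Such a difference enters a woman's ISMO-minus-NTG score with one sign in one order and the opposite sign in the other. The paired t test and the raw means do not separate it from the treatment effect. With equal orders it adds to the error variance. With unequal orders among the women analysed it also moves the estimate. The comparison matters because it determines which nitrate the main trial tests.

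**Working it through.** **Inputs from Section 2.5 (Pilot study).** "We wish to detect at least 15 units difference in headache score"; power 90%; two-sided alpha 0.05; SD 27.78; correlation 0.5 in the text; 20 women, raised by 10% to 22. The period effect D and the split between orders are not given and are assumed below.

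**The plan's own figure.** The Table 4A formula, with (1.960 + 1.282)² = 10.507, Δ = 15/27.78 = 0.540 and seven daily scores, gives 10.507 × (1 + 6 × 0.5)/(7 × 0.540²) = 20.6 with the text's correlation of 0.5, close to the stated 20; then 20 × 1.10 = 22. The 0.2 printed in Table 4A gives 11.3. That mismatch is a separate matter and is not used here.

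**Model.** Let τ be the true ISMO-minus-NTG difference and D the week-4 minus week-1 difference.

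- ISMO second (n1 women): expected within-woman difference τ + D.
- ISMO first (n2 women): expected within-woman difference τ − D.
- The mean over all n = n1 + n2 women has expectation τ + D(n1 − n2)/n.

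**Residual SD.** A paired t test with 20 women has 90% power at 15 points when the SD of the differences is 19.6. This value is back-solved from the plan's stated power, not quoted from it.

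**Equal orders, 10:10.** There is no bias. The SD seen by the paired test becomes √(19.6² + D² × 20/19).

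| D | SD of differences | Paired t power | Adjusted power | Paired t type I error |
|---|---|---|---|---|
| 0 | 19.6 | 90% | 90% | 0.05 |
| 5 | 20.3 | 89% | 90% | below 0.05 |
| 10 | 22.1 | 85% | 90% | about 0.03 |
| 15 | 24.9 | 77% | 90% | below 0.03 |

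Power and error rates are simulated. With an SD of 20.7 (normal approximation: 15 × √20/3.2415), paired power at 10:10 is 87%, 86%, 82% and 74% at D = 0, 5, 10 and 15, against 87% adjusted. The loss is of the same size.

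**Unequal orders, conditional on the split.** At 7:13 and D = 10 the shift is 10 × 6/20 = 3 points, or 20% of the 15-point target. Paired power is about 65% if the shift opposes the true difference and about 95% if it favours it, against 87% adjusted. Conditional type I error is about 0.066. If order were assigned by simple randomisation (an assumption), a split of 13:7 or worse among 20 women has probability 26%, and 14:6 or worse 12%.

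**Averaged over random allocation.** With each woman's order drawn at random, simulated paired t type I error is 0.05 at D = 0, 5, 10 and 15, and the estimate is unbiased.

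**Effect on the choice.** With τ = 15, D = 10 and an unfavourable 7:13 split, the standard error of the mean difference is 19.6/√20 = 4.39. The chance that the raw means point the wrong way is Φ(−12/4.39), about 0.3%. With τ = 0 and the same split, the raw-mean rule favours one product with probability Φ(3/4.39), about 75%, instead of 50%.

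**Cost of adjusting when D = 0.** Adjusted power is 90% at 10:10, 87% at 13:7 and 84% at 14:6, against 90% for the paired test: about 0, 3 and 6 points.

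**The case against.** The case for leaving the plan alone is substantial.

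- **No period effect is documented.** Section 2.1.2 reports that in the earlier trial women on ISMO who dropped out for headache did so within two days, and that headaches resolved within 24 hours of stopping. Nitrate habituation lasting to week 4 is not suggested. This stands, although it does not exclude expectation or diary effects. At D = 5 with equal orders the loss is about 1 point of power, and D = 15 makes the nuisance effect as large as the target.
- **No imbalance is documented.** How the order was generated is a detail that a journal article leaves to the full protocol, so its absence is not held against the plan. Imbalance could still arise by chance or from the washout exclusions. These may depend on which drug came first, and a paired test needs both weeks. Section 2.1.3 mentions ointment use in 18 pilot women against 22 planned, but does not say why or in which order they fell.
- **Randomising order already protects the test.** A reader might infer that the paired t test is generally biased or has inflated type I error. It does not: bias and a raised error rate appear only after conditioning on an unequal split, and with balanced orders the test is conservative.
- **The choice follows the lower mean, not the p-value.** A wrong pick is rare if the true difference is near 15 points. If it is near zero, the choice costs little in tolerability.
- **The pilot is finished and was significant.** Lost power no longer matters for that result. What remains is how the comparison is reported.

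**Conclusion.** The point holds as a modest, inexpensive improvement. The analysis and the selection rule ignore period in a design that randomises order. If a period effect exists, the general cost is power: about 1, 5 and 13 points at D = 5, 10 and 15 with 10:10 orders. With unequal analysed orders there is also a shift of D(n1 − n2)/n, conditional on the split. These sizes rest on an assumed D of 0 to 15 points, assumed splits, 20 women analysed, and an SD of 19.6 implied by the stated power.

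The documents do not support saying that the stated 90% power was missed, that the reported pilot result is biased, or that the wrong nitrate went forward. Each would need a non-zero D, and the last two also an unequal split; the documents show neither.

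**What to change.** In Section 2.6 (Pilot study), replace the paired t test with the period-adjusted crossover analysis. For each woman take the week-4 minus week-1 score, compare the two randomised orders by a two-sample t test, and halve the difference in means. The orders have expectations D + τ and D − τ, so D cancels. A linear model with woman, period and treatment is equivalent.

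In Section 2.4 (Pilot study), base the choice of nitrate on the adjusted treatment difference instead of the raw means.

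Because the pilot is complete, re-run the comparison this way on the existing diaries when reporting the result that supports the choice of NTG, and give the number of women analysed in each order. This needs no new subjects and no change to the conduct of the main trial. The price is one degree of freedom and the loss of power at D = 0 shown in the working, which grows as the orders become less equal.

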#### Main study

For all of the outcomes in our main study we will compare differences, at 27 months, between the intermittent nitrate group and the placebo group. To determine the percent change in total lumbar spine and hip BMD we will use a Student's t test. We will aim to have follow-up measurements on 100% of subjects randomized and plan to do an intention to treat analysis including measurements. To determine the percent change in BSAP and NTx we will use a repeated measures analysis of variance, after calculating the percent change in BSAP and NTx for each subject (see Table 4C). To determine if the incidence of headaches is higher in the intermittent nitrate group compared to the placebo group we will use a Student's t test. We will also use a Student's t test to determine if trabecular density by pQCT is higher in the intermittent nitrate group compared to the placebo group (Table 4B).

**Table 4C T6:** Method for calculated percent change in BSAP and NTx

We will calculate the percent change for BSAP* for each participant as:

Then we will average the percent change over all study participants

*We will perform identical calculations for NTx.

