We found that, compared with placebo, women randomized to intermittent ISMO at 20 mg had a 45.4% decrease in NTx (95% confidence interval [CI]: 25.8 to 64.9) and a 23.3% increase (95% CI: 8.9 to 37.8) in BSAP. Women randomized to intermittent ISMO at 5 mg had a 36.3% decrease in NTx (95% CI: 14.8 to 57.8) and a 15.9% increase in BSAP (95% CI: 1.1 to 30.7) (Figure 2) [30,31]. The decreases in NTx observed with 20 mg of ISMO are similar to those reported with alendronate, risedronate, and estrogen (about 50%) and greater than the 25% decreases reported with raloxifene [40,41]. However, all of the antiresorptive agents concomitantly decrease rates of bone formation. In contrast, we observed that treatment with ISMO resulted in significant increases in BSAP. The decrease in resorption, coupled with the increase in formation, suggests that ISMO may reduce fracture risk to an even greater degree than that seen with the current antiresorptive agents. The only adverse event was headache. Headaches, were more common among women randomized to ISMO (5 and 20 mg groups combined n = 55, 57%) compared with placebo (n = 2, 4%; p = 0.004). Headaches were no more common among women taking 20 mg of ISMO (n = 28) than among women taking 5 mg of ISMO (n = 27; p = 0.7).

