##### 2. Change from baseline in bone formation and bone resorption markers

Measuring markers of bone turnover will increase our understanding of the mechanisms by which intermittent nitrates increase BMD (i.e. a decrease in bone resorption and/or an increase in bone formation). We will measure bone turnover markers three months after initiating calcium and vitamin D because we expect a 10% decrease in markers with the use of supplements, and the maximal change in bone markers is typically observed at three months [36]. Thus, we will be assessing any additional effects of intermittent nitrates on markers of bone turnover in women receiving calcium and vitamin D supplements. Urinary NTx will be measured on a second morning urine sample using a monoclonal antibody technique (Osteomark) [73]. The intra-assay variability is 7.6% and the inter-assay variability is 4.0%. Serum BSAP will be measured on a fasting serum sample using a monoclonal antibody technique (Metra Biosystems) [74]. The intra-assay variability is 5.8% and the inter-assay variability is 5.2%. To minimize variability, subjects will be given written and verbal instructions on how to collect the second morning urine sample; for each subject we will collect all the samples (baseline, three, 12 and 24 month post randomization) at the same time, and we will store the blood and urine at -70°C and analyze all the samples together in a single laboratory. We will compare measures of bone turnover markers at 3, 12, and 24 months after randomization using a repeated measure of analysis of variance [75]. By measuring markers at three months we will be able to directly compare these results to the findings in our earlier study. By measuring markers at 12 and 24 months we will be able to evaluate to a limited degree, the question of tachyphylaxis with nitrates. Recall that in our earlier study we found a decrease in markers of bone resorption and an increase in markers of bone formation after 90 days of treatment with intermittent ISMO [30,31]. Measuring markers after one and two years of treatment will allow us to determine if there is still a marked decrease in bone resorption and increase in bone formation; no further changes in markers may indicate that the effects of nitrates on bone is transient.

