#### Main study

Our primary hypothesis is that, after 27 months, we will observe a clinically important and statistically significant increase in lumbar spine BMD, expressed in percent change from baseline, among women randomized to treatment compared with placebo. Our sample size calculation is based on t-test and will allow us to detect a 2% difference in spine BMD; 2% is the minimal difference that would justify nitrate treatment as this is the minimal magnitude of BMD change observed with other accepted osteoporosis treatments [5,61,62,78,79]. The standard deviation of change with a 2% difference in BMD ranges from 4.5% to 6.8% [5,59,62,80,81]. Assuming a standard deviation of change of 4.5%, a two sided alpha of 0.05 and a power of 0.90 we require 107 subjects per group [81].

The main trial will be preceded by a nitrate run-in phase and only women who complete the run-in phase will be entered into the main trial (see section 2.1aii). Our previous data indicate that 16 of 96 (17%) women randomized to ISMO dropped out due to headaches and 6 of the 144 (4%) women did not return to the study centre after randomization and were lost to follow up [42]. Thus we will "over recruit" by 25% to allow for a 17% drop out in the run-in phase due to headaches and a 8% loss to follow up during the main trial. Thus, we will recruit 280 subjects of whom we anticipate that 232 subjects will complete the run-in phase and enter the main trial (116 subjects per group). This sample size will ensure that we observe a clinically important and statistically significant difference between the active treatment and placebo group. Our sample size gives us adequate power to test our secondary hypotheses (Table 4B).

**Table 4B T5:** Required sample size to test all secondary hypotheses in main study.

Hypothesis	Clinically Important Difference	Standard Deviation of Change	Subjects, per group
Hip BMD will be higher in treatment group*	2%	4.5% (5, 59, 62, 80, 81)	107
NTx will lower in treatment group†	15% (69, 87–89)	28% (30, 35)	105
BSAP will be higher in treatment group†	15% (69, 87–89)	25% (30)	105
Headaches due to nitrates will be higher in treatment group**	20% (30)	5% (30)	36
Trabecular bone density by pQCT will be higher in treatment group**	10 mg/cm^3 ^(67, 70)	7.5 mg/cm^3 ^(67, 70)	31

* Based on a t-test, assuming a two sided alpha of 0.05 a power of 0.90 and a standard deviation of change in BMD measurements of 4.5%.

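### Bone markers (NTx, BSAP): averaged raw percent change is a valid but less efficient basis for comparing arms than a baseline-adjusted log-scale model, and it shifts within-arm means upward

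*Protocol article*

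**What the plan says.** The commitment is explicit in the protocol article.

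- Section 2.6, Main study: "we will use a repeated measures analysis of variance, after calculating the percent change in BSAP and NTx for each subject".
- Table 4C, after a formula that did not survive text extraction: "Then we will average the percent change over all study participants".
- Section 2.4, secondary outcome 2, names the visits: "We will compare measures of bone turnover markers at 3, 12, and 24 months after randomization using a repeated measure of analysis of variance". It also says the 12- and 24-month samples will help to judge tachyphylaxis, and that the three-month result will be compared directly with the earlier trial.
- Table 4B sizes the marker hypotheses for a 15% difference, with an SD of change of 28% for NTx and 25% for BSAP, and gives 105 women per group for each. Its footnote names repeated-measures ANOVA.
- Section 1.4 reports that women on ISMO 20 mg, against placebo, "had a 45.4% decrease in NTx (95% confidence interval [CI]: 25.8 to 64.9").

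The text shown mentions no log transformation and no baseline covariate for the markers.

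**The concern.** A percent change cannot fall below -100% but has no upper limit, and baseline enters only as a denominator. A woman whose baseline happens to be measured low contributes a large positive value. Two consequences follow.

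- The arithmetic mean within an arm lies above the typical change.
- Measurement noise at baseline is carried in full into the outcome, whereas a baseline covariate would remove part of it.

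NTx and BSAP are secondary outcomes, but they carry the mechanistic claim of less resorption and more formation. The question whether either change is still present at one and two years is likely to be read from within-arm means. The concern is therefore avoidable loss of precision and a distorted scale for those readings.

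**Working it through.** **1. The plan's own figure.** For two groups, n = 2(SD/δ)²(1.960 + 1.282)².

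- Primary BMD outcome: 2(4.5/2)² × 10.51 = 106.4, so 107, as stated.
- NTx: 2(28/15)² × 10.51 = 73.2, so 74.
- BSAP: 2(25/15)² × 10.51 = 58.4, so 59.

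Table 4B's 105 for both markers is not reproduced at 90% power, which is assumed here because its footnote gives none. It errs on the large side. At the stated SDs, 105 per group gives 97.3% power for NTx and 99.2% for BSAP in a simple comparison of percent change.

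**2. Within-arm shift (lognormal markers assumed).** Let w be the within-woman SD of the log marker and θ the true ratio to baseline. The mean observed ratio is θ·exp(w²). In an arm with no change, the SD of the ratio is exp(w²)·√(exp(2w²) − 1).

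| w | SD of percent change | Mean with no true change | Mean with a true 15% fall | Difference between arms |
|---|---|---|---|---|
| 0.17 | 25% | +2.9% | | |
| 0.19 | 28% | +3.7% | 0.85 × 1.037 = 0.881, so −11.9% | −15.6 points |
| 0.30 | 49% | +9.4% | 0.85 × 1.094 = 0.930, so −7.0% | −16.4 points |

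With no treatment effect the shift is the same in both arms and the difference is zero. With a true 15% fall, the between-arm fall is slightly overstated. Simulated type I error at SD 28% was 5.1%.

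**3. What SD is plausible?** From section 1.4's intervals: SE = half-width/1.96 and SD = SE/√(2/48). The 48 per arm is an assumption, from 144 women in three arms.

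- NTx, 20 mg: 19.55/1.96 = 9.97, giving SD 48.9%.
- NTx, 5 mg: 21.5/1.96 = 10.97, giving SD 53.7%.
- BSAP, 20 mg: 14.45/1.96 = 7.37, giving SD 36.1%.
- BSAP, 5 mg: 14.8/1.96 = 7.55, giving SD 37.0%.

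If only 40 ISMO and 46 placebo women were analysed (headache drop-outs removed, split evenly between doses), the SDs are about 46 to 51% for NTx and 34 to 35% for BSAP. Both ranges lie above Table 4B's values.

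**4. Efficiency.** On the log scale at one visit, adjusting for baseline multiplies the variance of a change score by (1 + ρ)/2, where ρ is the correlation of baseline with follow-up. The documents do not give ρ. For ρ of 0.8, 0.7 and 0.5 the factor is 0.90, 0.85 and 0.75. The NTx requirement of 74 becomes about 66, 63 or 55; the BSAP requirement of 59 becomes about 53, 50 or 44.

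**5. Power by simulation (lognormal markers).**

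- 15% difference, SD 28%, one visit, 107 per arm: 99% for raw percent change and 99% for log ANCOVA. Over three visits with some missing samples, SD 25 to 28%: 99.8 to 100% against 100%.
- 10% difference, SD 28%: a gain of about 3 to 8 points. A smaller run (500 repeats, so a standard error near 2 points for each power) with assumed missing samples and ρ of 0.5 to 0.8 gave 6 to 10 points at month 24. The gain is larger when ρ is lower.
- 15% difference, SD 49%, 107 per arm: 75 to 76% against 85 to 88% at one visit, and 91% against 97 to 98% averaged over three visits. The gain is about 6 to 13 points.

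**The case against.** The best defence is that the plan's test is sound. Mean percent change is a legitimate quantity, the shift cancels between randomised arms, and with more than 100 women per group moderate skewness (about 0.7 to 0.8 at Table 4B's SDs) does not disturb the test. At the planned difference and SDs, power is near 99% either way. Percent change is also the scale of the earlier trial, with which section 2.4 intends a direct comparison. All of this stands, and it limits the point to an improvement.

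The larger SD can be challenged too. It is back-calculated with an assumed number per arm, from a 12-week trial of oral ISMO, while Table 4B cites that trial for its own smaller values. That is fair, so the result is shown at both SDs.

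Two stronger readings are tempting, and the documents do not support them.

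- A reader might infer that the method favours an apparent rise in bone formation under nitrate. It does not do so between arms: the shift affects placebo equally. The +9% also belongs to an NTx-like SD. At the 36% implied for BSAP the same formula gives about +6%, again in both arms.
- A reader might infer that women with a missed visit are dropped, against intention to treat. A classical complete-case ANOVA would do that. With an assumed 8% lost after month 3 and 5% random misses per visit it would keep about 0.92 × 0.95³ = 79% of women. But the article excludes nobody and does not say how the model is fitted; that may sit in the full protocol or analysis plan.

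**Conclusion.** The point holds as a modest one about efficiency and scale. The article fixes raw percent change as the marker outcome, which gives a valid comparison with placebo but leaves the information in baseline partly unused.

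- Planned case (15%, SD 25 to 28%): about 1 point of power or less.
- Smaller effect (10%, SD 28%): about 3 to 8 points.
- Larger NTx SD (near 49%, 15% difference): about 6 to 13 points.

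Within arms, the means are about 3 to 4% too high at Table 4B's SDs and about 9% too high at an SD near 49%. At the larger SD a true 15% fall in NTx would appear as 7%, which matters when judging whether an effect has persisted.

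These figures rest on lognormal markers, an assumed baseline correlation and, for the larger SD, 48 women per arm in the earlier trial. The article reports no marker distribution. None of this touches the primary BMD analysis.

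**What to change.** In section 2.6, make the main marker analysis a mixed model for repeated measures on log(NTx) and log(BSAP) at 3, 12 and 24 months, with arm, visit, arm-by-visit interaction and log baseline, using every available sample. Report ratios of geometric means, converted to percent difference from placebo with 95% CI.

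The arm-by-visit term gives the between-arm effect at each visit, so persistence can be judged against placebo. It also lets the plan state whether the target is the final visit, as section 2.6 suggests ("For all of the outcomes in our main study we will compare differences, at 27 months"), or all three visits, as section 2.4 suggests.

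Keep the averaged raw percent change as a supporting summary, so that the three-month result stays comparable with the earlier trial.

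The cost is wording only: the baseline sample is already collected. The small downside is that the main estimate will be on a different scale from the earlier trial's.
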